### Demographics and study sites

Cameroon is a sub-Saharan African country. In 2010, there were 19,406,100 people distributed in 10 regions [3]. Data from routine antenatal screening indicates a HIV infection rate of 8.4% in 2011 among pregnant women. Furthermore, early diagnosis in infants born to HIV positive mothers showed a positivity rate of 7.1% [3]. The MORE CARE study research sites are located in two regions of Cameroon. The Essos National Insurance Fund Hospital is an urban setting located in Yaoundé, the administrative headquarter of the Centre Region and the political capital of Cameroon. It is situated in the Centre Region. The prevalence of HIV in Yaoundé is estimated at 6.4% in the population aged between 15 and 49 years old [21]. The Kousséri Regional Hospital and Goulfey District Hospital, which are respectively a semi-urban and a rural setting, are located in the Far North Region of Cameroon. This region has the lowest prevalence of HIV infection in Cameroon (1.2% in the population aged 15 to 49 years) [21]. The rate of loss to follow-up at sixth week after birth of children born to HIV infected mothers is 17.0% in the Centre region and 13.3% in the Far-North region, with a national prevalence of 35.1%. By twelve months of age, only 66% of these children are seen for serological diagnosis of HIV infection [3].

### Participants

We will include in the study all persons aged 18 years or older accompanying a HIV-infected or exposed child aged less than 15 years for HIV care and consenting to participate in the study. We will exclude to randomization i) subjects who do not have a mobile phone; ii) subjects whose follow-up appointment is scheduled in less than 3 days; and iii) subjects who are unable to communicate, read, or write in English or French.

### Reminder intervention

In the group receiving both SMS and phone calls (Group 4), the SMS reminder, in French or in English, will be sent between 08:00 and 12:00 AM, 72 hours before the appointment followed by a reminder phone call 48 hours before the appointment. The SMS will be sent manually. The SMS will serve as an appointment reminder and motivator. It will contain the date and the time of appointment, the location, and the name of the treating physician (Figure 3). To comply with medical confidentiality, the message will not contain any information on the health status of the child. Each text message sent will include about 300 characters including spaces. The method ‘message received’ will be used to ensure that the message was actually sent. For calls, a medical administrative assistant will phone 48 hours before the scheduled appointment, between 08:00 and 12:00 AM with communication in French or in English. A maximum of three calls attempts will be made. During the phone call, the medical secretary will remind the participant of the date and the location of his/her appointment and of the name of the treating physician. The name of the participant or the child will not be mentioned. In both SMSs and phone calls, communication is unidirectional towards the participant who cannot in return contact the medical secretary. This phone call procedure will be identical for the group receiving only phone calls (Group 3). Concerning the group receiving only the SMS (Group 2), the same procedure for sending SMS will be followed, and the SMS will be sent 48 hours before the appointment instead of 72 hours. It is important to note that, the content of communication (by SMS or by voice call) will be the same for all interventions.

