**Methods/Design:**

We will carry out a multicenter single-blind, randomized, factorial controlled trial. A randomization list will be electronically generated using random block sizes. Central allocation will be determined by sequentially numbered. A total of 224 subjects will be randomized into four groups (SMS, Call, SMS + Call, and Control) with an allocation ratio of 1:1:1:1. SMS and calls will be sent between 48 and 72 hours before the scheduled appointment. A medical assistant will send out text messages and will call participants. Our primary outcome is appointment measured by efficacy and efficiency of interventions. We hypothesize that two reminders (concomitant use of SMS and phone calls) as an appointment reminder is more effective to improve appointment compared to one reminder (only SMS or only call), and that the most efficient is use of only SMS. The analysis will be intention to treat.

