### Trial design

We will carry out a 2 x 2 factorial, multicenter randomized controlled trial, single-blind with an allocation ratio of 1:1:1:1 for adult-child pairs to four groups. Group 1 will serve as the control group and is composed of subjects provided an appointment and no reminder, reflecting the usual standard of care. Group 2 subjects will be provided an appointment and an SMS reminder. Group 3 members will be provided an appointment and a voice phone call reminder. Group 4 members will be provided both an SMS and a voice phone call reminder. A schematic of the groups and a study diagram according to the recommendations of the Consolidated Standards of Reporting Trials (CONSORT) [19] are shown in Figures 1 and 2 respectively. The study will be performed for 5 months, from January to May 2013.

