**Primary**				
Presence at appointment				
• Efficacy	Nominal	Binary	% present at appointment	Chi-square test
				Additive and multiplicative scales for synergy measurement
• Efficiency	Ratio	Continuous	Mean of efficiency	*T*-test
- Working time	Ratio	Continuous	Mean of working time	*T*-test
- Financial cost	Ratio	Continuous	Mean of financial cost	*T*-test

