#### Sample size

The primary objective is to measure the patient presence at their scheduled appointment. The calculation of the sample size will be based on the comparison of proportions of presence at appointment. The value of alpha is 0.05. The test is two-tailed. We assume that the presence at appointments using SMS as reminder and phone calls is, respectively, 59.0% and 59.6% [11]. We also assume that the difference would be 25% between the group that will receive both SMS and phone calls and the groups that will receive only an SMS or only phone calls. The minimum size of the sample required will be 50 subjects in each group for analysis by intention to treat with 80% power and a significance level of 0.05. We will exclude from analysis the participants with incomplete data. For this we assume a 10% attrition rate. Thus, we will need 224 subjects (56 in each group). WinPepi has been used to calculate the size of the sample [20].

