### Analysis plan

Data will be coded, entered, and analyzed using the Statistical Package for Social Science (SPSS) version 20.0 for Windows (SPSS, Chicago, Illinois, USA). We will describe continuous variables using means with standard deviations, and categorical variables using their frequencies and percentages. We will use the principle of ‘intention to treat’ analysis. The risk ratio will be used to measure effect of interventions on proportion of presence at medicals appointments and will be expressed with 95% confidence interval. The *t*-test will be used to compare quantitative variables, and the chi-square test will be used to compare qualitative variables. A *P* value less than 0.05 will be considered statistically significant. WinPepi will be used to measure the interaction between SMS and call in the group receiving both call back methods of appointment.

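### The SMS is sent at 72 h in Group 4 but at 48 h in Group 2, so the planned SMS-by-call interaction cannot be read as synergy from combining channels

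*Protocol article*

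**What the plan says.** Under Trial design the protocol article describes a 2 x 2 factorial trial with four equal groups: control, SMS, call, and both. It says there that "Group 4 members will be provided both an SMS and a voice phone call reminder", without giving the timing.

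The timing is fixed under Reminder intervention:

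- Group 4: the SMS goes out "72 hours before the appointment followed by a reminder phone call 48 hours before the appointment".
- Group 3: the same call procedure as Group 4, so the call is at 48 h.
- Group 2: "the SMS will be sent 48 hours before the appointment instead of 72 hours".

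What that section says is held the same across interventions is the content of the message, not its timing.

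Table 1 lists "Additive and multiplicative scales for synergy measurement" under the primary efficacy outcome. The Analysis plan adds that "WinPepi will be used to measure the interaction between SMS and call in the group receiving both call back methods of appointment". The Discussion presents a possible synergy between text message and call as something this trial, unlike earlier studies, will measure. The Abstract states the hypothesis that "two reminders (concomitant use of SMS and phone calls) as an appointment reminder is more effective to improve appointment compared to one reminder".

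**The concern.** To read a factorial interaction as synergy, the SMS must be the same intervention whether or not a call is also made. Here it is not. Group 4 v Group 3 shows the effect of a 72 h SMS added to a call, while Group 2 v Group 1 shows the effect of a 48 h SMS with no call. The interaction is the difference between these two effects, so it mixes the presence of the call with the change in SMS lead time.

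An apparent synergy could come from combining two channels, or from an earlier SMS and two contacts a day apart. An apparent antagonism has the same ambiguity. For the same reason, Group 4 v Group 2 is not the pure effect of adding a call. At stake is a conclusion that is listed under the primary outcome and offered as the trial's novelty.

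**Working it through.** **1. Schedules side by side** (Reminder intervention)

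| Group | SMS | Call |
|---|---|---|
| 1 Control | none | none |
| 2 SMS | 48 h | none |
| 3 Call | none | 48 h |
| 4 SMS + call | 72 h | 48 h |

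**2. What the interaction estimates.** Let G1 to G4 be the attendance proportions.

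- Additive scale: (G4 − G3) − (G2 − G1) = [G4 with SMS at 48 h − G3 − G2 + G1] + [G4 with SMS at 72 h − G4 with SMS at 48 h]. The first bracket is synergy of channels at equal lead time. The second is the lead-time effect when a 48 h call is also made.
- Multiplicative scale: G4 × G1 / (G2 × G3) equals the equal-lead-time ratio multiplied by (G4 with SMS at 72 h) / (G4 with SMS at 48 h).

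**3. Can the two parts be separated?** Write a model with five terms: intercept, SMS, call, SMS x call, and SMS at 72 h. The rows are:

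- Group 1: (1, 0, 0, 0, 0)
- Group 2: (1, 1, 0, 0, 0)
- Group 3: (1, 0, 1, 0, 0)
- Group 4: (1, 1, 1, 1, 1)

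The last two columns are identical, so the rank is 4 with 5 terms. Without an outside assumption about lead time, no analysis of these four groups can separate them.

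**4. The plan's own sample size.** Under Sample size, attendance is 59.0% with SMS and 59.6% with a call, and "the difference would be 25% between the group that will receive both SMS and phone calls" and the single-reminder groups. For 59.0% v 84.0%, two-sided alpha 0.05, 80% power, pooled variance:

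n = [1.960 × √(2 × 0.715 × 0.285) + 0.842 × √(0.59 × 0.41 + 0.84 × 0.16)]² / 0.25² = 50 per group.

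Then 50 / 0.9 = 55.6, rounded up to 56, and 56 × 4 = 224. The plan's figures reproduce. They rest on pairwise comparisons and do not involve the interaction.

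**5. Precision of the interaction.** Inputs: G2 = 0.59, G3 = 0.596, G4 = 0.59 + 0.25 = 0.84. The Sample size section gives no figure for G1; I assume 0.35 to 0.55, so that single reminders do better than, or close to, control.

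- Additive SE = √(Σ p(1 − p)/n). For groups 2 to 4, Σ p(1 − p) = 0.2419 + 0.2408 + 0.1344 = 0.6171. G1 adds 0.2275 (at 0.35) up to 0.25 (at 0.50).
  - n = 50: SE 0.130 to 0.132; half-width 1.96 × SE = 25.5 to 25.8 points.
  - n = 56: SE 0.123 to 0.124; half-width 24.1 to 24.4 points.
- Log-ratio SE = √(Σ (1 − p)/(np)).
  - n = 50: 0.218 to 0.262; the 95% interval is the estimate divided and multiplied by exp(1.96 × SE) = 1.53 to 1.67.
  - n = 56: 0.206 to 0.247; factor 1.50 to 1.62.

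**6. Illustrative shift (assumed, not from the protocol).** A lead-time effect of 2 to 5 points moves the additive estimate by 2 to 5 points. It multiplies the ratio by 0.84/0.82 = 1.024 to 0.84/0.79 = 1.063. The shift does not depend on n.

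**7. For contrast.** Group 4 v Group 2 as whole strategies: difference 25 points, 95% half-width 1.96 × √((0.2419 + 0.1344)/50) = 17.0 points. This comparison stays valid.

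**The case against.** The strongest reply is that the trial is pragmatic. Study objectives asks which reminder method is best, which is a comparison of strategies as delivered. The stated hypotheses do not mention synergy, and the Discussion calls it only possible. Each schedule is disclosed, and spacing two contacts while placing the last one at 48 h in every reminder group is a defensible design. All of this stands, and it limits the point to interpretation. It does not rescue the synergy reading, which Table 1 places under the primary outcome.

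A second reply is that the lead-time effect may be small beside a half-width of about 25 points. That is fair, and no size is claimed. But imprecision and non-identification are different problems, and only the first shrinks with more participants.

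A third reply concerns the assumed control rate. Background reports 65% of infants presenting at six weeks. Under Demographics and study sites, loss to follow-up of 17.0% and 13.3% in the two study regions implies about 83% to 87% seen. With G1 from 0.65 to 0.867 and n = 50, the half-width becomes 23.7 to 25.5 points and the ratio factor 1.44 to 1.49. Those control rates would exceed the plan's own 59.0% and 59.6% for single reminders, so they fit its assumptions poorly. The aliasing in steps 2 and 3 does not depend on G1.

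Finally, the Abstract says reminders go out between 48 and 72 hours before the visit. That is compatible with the schedules but does not show which group gets which timing.

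**Conclusion.** The concern holds. SMS lead time is completely aliased with the SMS-by-call combination, so neither the additive nor the multiplicative measure can be interpreted as synergy of channels. A later analysis plan cannot repair this, because it follows from the delivered schedule.

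The consequence is narrow. Group 4 against Groups 1, 2 and 3 remain valid randomized comparisons of whole strategies, and the two-versus-one hypothesis and the sample size stand. The amount of distortion is unknown in size and direction; the 2 to 5 point figure is illustrative only. The identification result rests only on the schedules in Reminder intervention. The precision figures rest on the plan's assumed rates and the assumed control rate. The text should be corrected, because as written it promises a conclusion the design cannot support.

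**What to change.** Trial status says recruitment is ongoing, so keep the delivered schedule and the four groups, and change the wording:

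1. In Table 1 and the Analysis plan, state that the interaction is between the reminders as scheduled, including the earlier SMS in Group 4. State also that it will not be interpreted as synergy from combining channels, nor Group 4 v Group 2 as the pure effect of adding a call.
2. Change the Discussion sentence on synergy to match.
3. Helpful but not essential: in the Abstract and Trial design, describe Group 4 as a staggered two-contact strategy (SMS at 72 h, then call at 48 h). The word concomitant in the Abstract hides the 24 h gap.

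Procedures, allocation and sample size do not change. The cost is giving up the channel-synergy claim, which these groups could not have supported.

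Equal SMS lead time in Groups 2 and 4 would have avoided the problem before recruitment, and it was feasible: Participants excludes appointments less than 3 days away. Each option had a price. Both at 48 h loses the spacing in Group 4; both at 72 h loses the match at 48 h between SMS only and call only. I do not propose either as a mid-trial change.

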**Figure 3 F3:**
[figure not shown]
**Text message.** We will send this text message to all participants who allocate to Group 2 (text message (SMS)) and Group 4 (SMS + call).

### Control

The control group (Group 1) will receive neither SMS nor phone calls, reflecting the usual practice of care.

### Study objectives

The objective of this trial is to determine which reminder - SMS, phone call, or both SMS and phone calls - is the optimal method to increase HIV-infected and HIV-exposed children’s attendance at medical appointments (effectiveness) and which is the most efficient related to working time and financial cost (efficiency).

### Outcome measures

#### Primary outcomes

Table 1 shows an overview of the outcomes and statistical method that will be used. The primary outcome will be the presence at appointment. It will be measured by effectiveness, and efficiency related to both financial cost and working time. Effectiveness will be the capability of producing a presence at an appointment (attendance). We will measure three aspects of efficiency using the following ratios: i) presence at appointment/financial cost x working time; ii) presence at appointment/financial cost; and iii) presence at appointment/working time. Time for text message intervention will be measured from the start of writing the message until the sending. For phone calls, this time measure will begin when we make the first call (not when the participant picks up the phone) and will stop at the end of the communication. The cost of each call and SMS will be evaluated using a prepaid plan. The prepaid plan means that the phone will have a financial amount of communication known before the call. After call, the difference will be made with the remaining amounts. Each SMS will cost 50 or 100 Francs of Financial Community of Africa (FCFA) (approximately 0.076 € or 0.152 €).

**Table 1 T1:** Overview of outcome measures

**Outcomes measures**	**Scale**	**Type**	**Measure**	**Analysis method**

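### The efficiency ratios divide total attendance, not attendance gained over control, by cost or time, so they can misrank the reminders; ratio (i) as printed also rewards slower work

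*Protocol article*

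**What the plan says.** The section on primary outcomes measures presence at the appointment in two ways, effectiveness and efficiency. For efficiency it states: "We will measure three aspects of efficiency using the following ratios: i) presence at appointment/financial cost x working time". Ratios (ii) and (iii) are presence over cost and presence over working time. Table 1 lists efficiency under the primary outcome, summarised as a mean and compared by t-test. No control-arm term appears in any ratio.

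On the reference arm, the Control section says: "The control group (Group 1) will receive neither SMS nor phone calls, reflecting the usual practice of care". The Abstract's hypothesis is that "the most efficient is use of only SMS".

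An SMS costs 50 or 100 FCFA. The cost of a call is read from the fall in the prepaid balance, and no figure is given. SMS time runs from starting to write until sending. Call time starts at the first call and stops when the communication ends. Under Reminder intervention, "A maximum of three calls attempts will be made".

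**The concern.** Some children attend without any reminder. A ratio with total attendance on top counts those visits as a product of the reminder. Two arms with the same attendance are then ranked by price alone, even if neither reminder changed anything. An effective but dearer reminder can fall below an ineffective cheap one.

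Efficiency is half of the stated objective, and the expected winner, SMS alone, is the arm that presence/cost tends to favour. A finding that SMS is most efficient on that ratio would therefore be weak evidence that SMS buys attendance cheaply. The control arm could answer that question, but the ratios do not use it.

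Ratio (i) has a separate problem. As typeset it is (presence/cost) × time, which rises as staff take longer. Presence/(cost × time) was probably meant, and the two can order the arms differently.

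**Working it through.** **Inputs from the article.** SMS 59.0%, Call 59.6% (Sample size); "the difference would be 25% between the group that will receive both SMS and phone calls" and those given one reminder; SMS 50 or 100 FCFA. **Assumed, because the article gives no figure:** control attendance p0 and call cost c.

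**1. The plan's own figure.** The sample-size section says "The value of alpha is 0.05. The test is two-tailed" and "The minimum size of the sample required will be 50 subjects in each group for analysis by intention to treat with 80% power". Reading the 25% as percentage points gives 84% for SMS + Call. With mean proportion 0.715:

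n = [1.960·√(2·0.715·0.285) + 0.842·√(0.59·0.41 + 0.84·0.16)]² / 0.25² = 50 per group.

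Then 50/0.9 rounds up to 56, and 4 × 56 = 224. Both figures are reproduced. A relative 25% would need 160 per group, so 84% is the rate the plan used. This calculation rests on attendance only.

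**2. Presence/cost with no reminder effect.** If attendance is p in every arm, the ratio is p/cost, and SMS beats SMS + Call at any positive call price. For example, an ineffective SMS (p = p0 = 55%, 50 FCFA) scores 0.55/50 = 11.0 per 1000 FCFA. An effective combination (84%, 50 + 100 = 150 FCFA) scores 0.84/150 = 5.6. Visits gained per 1000 FCFA are 0 and (0.84 − 0.55)/150 = 1.93.

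**3. Break-even on the plan's rates.** With SMS cost s, SMS + Call beats SMS on presence/cost when 0.84/(s + c) > 0.59/s, that is c < s(0.84/0.59 − 1) = 0.42s. This is 21 FCFA for s = 50 and 42 FCFA for s = 100. On visits gained the condition is c < s[(0.84 − p0)/(0.59 − p0) − 1].

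| p0 (assumed) | Limit on visits gained, s = 50 | Limit, s = 100 |
|---|---|---|
| 30% | 43 | 86 |
| 40% | 66 | 132 |
| 50% | 139 | 278 |
| 55% | 313 | 625 |

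The order reverses for any call cost between 21 (or 42) FCFA and the limit in the table.

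**4. Worked case, s = 100, c = 150.**

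| Arm | Cost | Presence per 100 FCFA | Gained per 100 FCFA, p0 = 50% | Gained per 100 FCFA, p0 = 40% |
|---|---|---|---|---|
| SMS | 100 | 0.59 | 0.09 | 0.19 |
| Call | 150 | 0.397 | 0.064 | 0.131 |
| SMS + Call | 250 | 0.336 | 0.136 | 0.176 |

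At p0 = 50% the combination moves from last to first. At 40% SMS stays first and the combination moves to second. For these prices the switch is where 100(0.84 − p0) = 250(0.59 − p0), so p0 = 63.5/150 = 42%.

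As cost per additional attendance at p0 = 50%: SMS 100/0.09 = 1111 FCFA; SMS + Call 250/0.34 = 735 FCFA; moving from SMS to SMS + Call 150/0.25 = 600 FCFA.

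**5. Ratio (i).** With assumed times of 2, 3 and 5 minutes and the costs above, (P/C) × T, times 1000, is 11.8 (SMS), 11.9 (Call) and 16.8 (both). P/(C × T), times 1000, is 2.95, 1.32 and 0.67. The two readings give opposite orders.

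**6. Call clock.** Assume 0.5 minutes per attempt and 2 minutes of talk. Three attempts take 3 × 0.5 + 2 = 3.5 minutes of handling. Read literally, the clock shows 3.5 minutes if they run back to back and 33.5 minutes if there are 15-minute gaps. The article fixes no spacing. It also gives no stop time for a participant who is never reached, a case foreseen under Secondary outcomes.

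**The case against.** The strongest reply is that the objective asks which of the three reminders is most efficient, so Group 1 need not be scored. That stands. A reader might infer that division by zero in the control arm is itself the defect, but the article's wording confines efficiency to the reminders. What remains is that the control arm is also unused as a baseline.

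A reader might also infer that the measures favour SMS whatever happens. The documents support this for presence/cost only. No handling times are given, the SMS is typed by hand at about 300 characters, and ratio (i) read literally can put the combination first.

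Reversal needs the full 25-point gain and a suitable pair of unstated inputs. SMS against Call seldom changes order, since their assumed rates differ by 0.6 points.

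The choice of starting the clock before the participant answers suggests that the aim was to count dialling and ringing, which is legitimate. Large clock errors depend on invented spacing. A t-test on per-person ratios, with every absentee at zero, is an awkward summary, but no wrong ranking follows from it without an assumed spread.

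Table 1 already reports attendance, mean cost and mean time separately, so the ingredients of a better measure are planned.

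Finally, the incremental ratio has its own weakness. At 50% v 59% with 56 per arm, SE = √[(0.25 + 0.2419)/56] = 0.094 and z = 0.09/0.094 = 0.96, so about 17% of trials would show no SMS gain (about 33% at control 55%). If control attendance were 65%, the Background figure for a different visit, the assumed SMS gain would be negative.

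**Conclusion.** The point holds in a limited form. As defined, the efficiency ratios credit reminders with visits that would have occurred anyway, and this is true in every scenario. On presence/cost an ineffective cheap reminder can outrank an effective dearer one. On the plan's rates the combination needs a call priced below 42% of an SMS to come out ahead.

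Misranking of SMS against SMS + Call is possible, not established. With SMS at 100 FCFA it occurs for call costs from 42 FCFA up to 132 FCFA (control 40%) or 278 FCFA (control 50%), given 59% and 84% attendance. It would be wrong to say that the order always reverses, since control attendance and call cost are not in the article. Ratio (i) as printed multiplies by time and needs correcting on any reading. The call clock is a lesser matter of definition. The attendance analysis and the 224 participants are not affected.

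**What to change.** - Base the efficiency conclusion on arm-level incremental measures: difference in mean cost, and separately in mean staff time, divided by the difference in attendance proportion. Compute them for each reminder arm against Group 1 and between reminder arms.
- Give bootstrap confidence intervals by randomised arm. Report the differences in cost, time and attendance beside each ratio, because the ratio is unstable when the gain is near zero or negative.
- Drop ratio (i), or write it as presence/(cost × time).
- Define call time as the sum of dial-to-hang-up time over all attempts, unanswered ones included. Gaps are then not counted, and unreached participants have a value.

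Moving efficiency below attendance in the outcome hierarchy is an option with trade-offs, and this point does not require it.

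The cost is revised analysis wording, a short bootstrap program and a per-attempt time log. Attendance, cost and time are already being collected. The downside is wide or unbounded intervals when the attendance gain is small.

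### Efficiency ratio (i), even when bracketed, divides by cost times time; this inflates the combined arm's disadvantage and ranks SMS against Call without regard to what a staff minute costs

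*Protocol article*

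**What the plan says.** Under Primary outcomes, the protocol article defines the primary outcome as presence at the appointment and adds: "It will be measured by effectiveness, and efficiency related to both financial cost and working time". Three ratios are listed. The first is "presence at appointment/financial cost x working time"; the others are "ii) presence at appointment/financial cost; and iii) presence at appointment/working time". Table 1 plans a mean of efficiency compared by t-test, and also lists mean working time and mean financial cost. Study objectives asks which of SMS, call or both is most efficient in working time and money. The Abstract expects SMS alone to be the most efficient.

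On the inputs: "The cost of each call and SMS will be evaluated using a prepaid plan", and "Time for text message intervention will be measured from the start of writing the message until the sending". An SMS is priced at 50 or 100 FCFA. No call cost, no working time and no pay rate is given.

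Under Trial design, "Group 4 members will be provided both an SMS and a voice phone call reminder". Reminder intervention adds that the call procedure is the same in Groups 3 and 4, and that the SMS procedure in Group 2 differs from Group 4 only in timing.

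**The concern.** Ratio (i) is the only one of the three that brings cost and time together, and it does so by multiplying them. A participant in Group 4 uses the francs of an SMS plus those of a call, and the minutes of an SMS plus those of a call. The product of those two sums contains cross terms (SMS cost × call time, call cost × SMS time) that correspond to no resource anyone spends. The unit, attendances per franc-minute, has no evident use in a decision.

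This is separate from the missing brackets. Read strictly left to right, the printed formula would multiply by time and so reward slower work. The point here takes the charitable reading, presence/(cost × time).

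At stake are how far the combined arm appears to fall short on a component of the primary outcome, and whether the SMS v Call order on that component agrees with what the two reminders actually cost.

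**Working it through.** **Inputs.** Attendance of 59.0% (SMS) and 59.6% (Call), and a 25-point gain for SMS + Call, hence 84.0% and 84.6% (Sample size). SMS price 50 or 100 FCFA (Primary outcomes). Call cost, both working times and pay per minute are not in the document and are assumed wherever used.

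**The plan's own figure.** No value is stated for any efficiency ratio. The sample size reproduces: 59.0% v 84.0%, two-sided 0.05, 80% power, no continuity correction, gives 50 per group; 59.6% v 84.6% also gives 50. Then 50/0.9 = 55.6, rounded up to 56, and 4 × 56 = 224. This confirms that the 25% is meant as percentage points.

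**Step 1: charge to the combined arm.** Let cS, tS and cC, tC be the cost and time of SMS and Call. Group 4 uses cS + cC and tS + tC.

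- Product: (cS + cC)(tS + tC) ≥ (√(cS·tS) + √(cC·tC))² ≥ 4 × min(cS·tS, cC·tC).
- Sum, with w the price of a minute: (cS + w·tS) + (cC + w·tC) ≥ 2 × the smaller of the two parts.

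Example: two identical reminders of 50 FCFA and 3 min. The product gives (50 + 50)(3 + 3) = 600 against 150 for one, a factor of 4, although exactly twice the resources were used. Over 1,000,000 assumed sets (SMS 50 or 100 FCFA, call 10 to 400 FCFA, each time 0.25 to 6 min) the product factor had minimum 4.00 and median 9.2.

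**Step 2: score at the planned rates.**

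| Denominator | Minimum charge | Score relative to better single reminder | Attendance needed to tie |
|---|---|---|---|
| cost × time | 4 | at most (0.84/0.59)/4 = 0.36 | at least 4 × 59% = 236% |
| sum (also ratios ii and iii) | 2 | at most (0.84/0.59)/2 = 0.71 | at least 2 × 59% = 118% |

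**Step 3: individual ratios.** If efficiency is computed per participant and averaged, write a = cS·tS and b = cC·tC for one person. Then 1/((cS + cC)(tS + tC)) ≤ 1/(4√(ab)). By Cauchy-Schwarz the mean of the right side is at most one quarter of √(mean(1/a) × mean(1/b)), so at most one quarter of the larger single-arm mean. The 4-fold bound therefore carries over, but only if attendance is independent of cost and time, so that it factors out. Simulated under that condition, the smallest factor was 4.4.

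**Step 4: SMS v Call.** Multiplying every time by w scales both products by w, so their order never changes. Under a sum it can. Assume SMS 50 FCFA/3 min, call 100 FCFA/1 min and equal attendance.

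- Product: 50 × 3 = 150 and 100 × 1 = 100, so the call is preferred at every w.
- Total cost: 50 + 3w against 100 + w, equal at w = 25. At w = 10 it is 80 v 110 (SMS preferred); at w = 30 it is 140 v 130 (call preferred).

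Over the same assumed sets, with w from 0 to 200 FCFA/min, the cheaper reminder by total cost differed from the one with the smaller product in 8% to 21% of cases.

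**The case against.** Much of the opposing case stands.

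- **The combined arm cannot win under the proposed measure either.** This is correct. A reader might infer from the 236% figure that ratio (i) alone shuts SMS + Call out. The planned gain is 0.84/0.59 = 1.42-fold, below even the factor of 2 that a sum imposes, so ratios (ii), (iii) and total cost exclude it too. Only the margin is distorted.
- **Ratio (i) is not named as decisive.** Also correct. The three ratios are presented as aspects of efficiency. It is tempting to treat (i) as the one that answers the objective, but the text does not say so. Ratios (ii) and (iii) would reveal any case where one reminder is cheaper and the other faster, and with the mean cost and mean time in Table 1 a reader could build a total cost.
- **The SMS v Call reversal rests on assumed inputs.** Correct. If one reminder is both cheaper and faster, then at equal attendance every measure agrees. The documents show that a conflict is possible, not that it is likely.
- **The product does not fix one exchange rate between francs and minutes.** Correct. Its ranking is unaffected by rescaling either unit, and its implied trade-off shifts with the data. The fault is that it ignores the price of a minute.
- **The 4-fold bound is conditional for individual ratios.** Correct. Independence is doubtful, since an answered call may both last longer and raise attendance.

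None of this justifies multiplying. The article gives no reason for it, and the cross terms remain.

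**Conclusion.** The point holds in limited form. Ratio (i) is a badly constructed joint measure within the primary outcome. At arm level it at least quadruples the combined arm's charge where the resources used at least double. At the planned rates this lowers the ceiling on its relative score from about 0.71 to about 0.36. It is also indifferent to the price of staff time when ordering SMS and Call, and so can disagree with their total cost.

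The arm-level bound assumes that Group 4's cost and time are the sums of the single-reminder values, which the Reminder intervention section supports. If the better single reminder is chosen by the full ratio at 59.0% v 59.6%, the factor slips only to about 3.98. The document does not support saying that ratio (i) uniquely rules out the combined arm, or that a wrong SMS v Call conclusion is to be expected. The attendance comparison and the sample size are unaffected.

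**What to change.** Replace the denominator of ratio (i) by a total cost per participant in FCFA: phone cost + working minutes × the assistant's pay per minute. State the pay rate and its source, and repeat the comparison over a range of plausible rates, giving the rate, if any, at which the SMS v Call order changes. Keep ratios (ii) and (iii) as components.

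The cost is one pay figure and a line of analysis text. Francs and minutes are already to be recorded, so no further data collection from participants and no change in sample size is needed. The downside is that the combined result will depend on a pay rate that the protocol does not give, which is why the sensitivity range is part of the change. The fix will not make SMS + Call the most efficient arm at the planned rates; it will report its shortfall at its proper size.
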